#### Contact moments

The study consists of five contact moments for parents in the intervention group:
T0.0: baseline - visit to the dental practice:Baseline data collection; first interview, including identification of a barrier, discussion of a possible strategy and agreement on an action point.T0.1: 1 month after T0.0 - visit to the dental practice (parent only):Second interview, including follow-up on the progress with the first action point, identification of a second barrier (if present), discussion of a possible strategy and agreement on a second action point.T0.2: 1 month after T0.2 – telephone recall:Telephone recall to follow-up on the progress with the first and second action points.T1: 6 months after T0.0 – visit to the dental practice:Follow-up data collection.T2: 24 months after T0.0 – visit to the dental practice:Follow-up data collection.

Where possible, the research visits at the dental practice will be combined with a regular dental check-up. Parents in the control group will visit the dental practice only at T0.0, T1 and T2 for baseline and follow-up data collection. The interval between T0.0 and T1 is allowed to deviate by 2 months, and the interval between T1 and T2 may vary with 3 months. If parents miss their appointment at T1 and T2, or at T2 only, they will be treated as dropouts. If they only miss the appointment at T1, missing data for T1 will be imputed. Missed telephone recalls will be documented to account for this in the analysis.

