#### Clinical outcome: children’s dental caries experience

At T2, a clinical oral examination will be performed to assess children’s dental caries experience. The clinical oral examination will only include a visual inspection and no x-rays will be taken. Dental caries status will be assessed using the merged International Caries Detection and Assessment System (ICDAS) coding system [35], which classifies dental caries into sound (‘0’), initial stage of decay (‘A’), moderate decay (‘B’) or extensive decay (‘C’). In addition, the dmfs-index will be scored according to WHO Basic Methods for Oral Health Surveys [36]. The oral examinations will be performed by one dentist from each control or intervention practice, after they have received training from a certified ICDAS trainer for calibration and standardisation purposes. The training will be organised 23 months after inclusion of the first participants. During the training, the dentists’ intra- and inter-examiner reliability will be assessed; a minimum weighted kappa of 0.60 for both the intra and inter-examiner reliability is required to certify as an examiner [37]. In case of lower reliability scores, more training will be provided. The dmft and dmfs at baseline will be extracted from personal dental health records from the dental practice, in order to compare differences in dental caries experience between intervention and control children at baseline, and to adjust for potential differences in the analysis.

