### Statistical analysis

All data will be coded with a unique ID, and data will be securely stored at the Department of Social Dentistry at ACTA. The analysis will be performed in STATA. Differences in the primary outcome (dmfs and the combined ICDAS scores ‘B and C’ and ‘A, B and C’) between children in the intervention and control group at T2 will be analysed using zero-inflated Poisson or negative binomial regression. Baseline differences in children’s dmft scores (obtained from dental records) will be taken into account.

Differences in the three tooth brushing-related outcomes between children in the intervention and control group at T1 and T2 will be analysed using ordered logistic or logistic regression (for tooth brushing frequency in children; either treated as a ordinal variable or dichotomous variable, depending on the distribution of responses), and linear or negative binomial regression (for parental self-efficacy scores and children’s plaque scores).

All analysis will be adjusted for clustering of observations within dental practices. In case of significant differences in co-variates (moderators) between the intervention and control group at baseline (T0), the analysis will be adjusted accordingly for these co-variates, or in case of sufficient power, a sub-group analysis will be performed. An intention-to-treat analysis will be conducted to account for participants that will be lost to follow-up. Statistical significance is set at α = 5%.

Qualitative data from the focus group interviews and telephone interviews will be processed using the Maximised Qualitative Data Analysis programme (Verbi-software MAXQDA). Conventional content analysis will be used to identify emergent themes and concepts related to the feasibility and acceptability of the intervention.

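### The T2 tolerance is tied to T1, so the 24-month caries examination may fall at 19 to 29 months, and the stated adjustment rule cannot correct for its timing

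*Protocol article*

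**What the plan says.** Contact moments gives the nominal times as "T1: 6 months after T0.0" and "T2: 24 months after T0.0". The tolerances are attached to successive intervals: the one from T0.0 to T1 is "allowed to deviate by 2 months, and the interval between T1 and T2 may vary with 3 months". No tolerance is given for the interval from T0.0 to T2. On missed visits the same section says: "If they only miss the appointment at T1, missing data for T1 will be imputed". Such a child stays in the study.

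Outcome measures defines the primary outcome as caries experience after 24 months, measured at T2, and sets success at a 25% reduction, equated there with 1.5 to 2.0 dmfs.

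The section on the clinical outcome has one dentist per practice do the examination after ICDAS training, with a weighted kappa of at least 0.60 needed to certify. On the date it says: "The training will be organised 23 months after inclusion of the first participants".

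Statistical analysis compares T2 caries by zero-inflated Poisson or negative binomial regression, taking baseline dmft and clustering into account. Other covariates are conditional: the rule opens with "In case of significant differences in co-variates (moderators) between the intervention and control group at baseline (T0" and adjusts only then. Co-variates lists the child's age among variables that need adjustment.

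**The concern.** The dmfs count is cumulative, so a child examined later has had longer to accrue affected surfaces. If the date of examination can vary widely, and could vary differently in the two groups, part of any difference in dmfs may reflect timing rather than the intervention.

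Three features make this more than a formality. Practices are not randomised, so nothing balances scheduling habits between groups. The practices that schedule the visits know their group. Visits are combined with regular check-ups where possible, and check-up intervals are shorter for children at increased caries risk, so timing may vary with practice and with risk. Any timing difference would pass directly into the primary contrast and the 25% success rule.

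**Working it through.** **1. The window.** The plan's own figure is T2 at 24 months, which with T1 at 6 months implies a nominal T1 to T2 interval of 24 − 6 = 18 months. The plan states no outer limits for T2, so they have to be derived.
- T1 = 6 ± 2, so 4 to 8 months.
- T1 to T2 = 18 ± 3, so 15 to 21 months.
- Earliest T2 = 4 + 15 = 19 months. Latest T2 = 8 + 21 = 29 months. Span: 10 months.
- If the 3 months are a total spread (±1.5), the range is 4 + 16.5 = 20.5 to 8 + 19.5 = 27.5 months.
- For comparison, ±3 months set directly on T0.0 gives 21 to 27 months.

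A child without a T1 visit keeps the nominal 24-month date, but neither interval tolerance can be applied to it.

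**2. Against the training date.** For a child enrolled e months after the first inclusion, the T2 window opens at study month e + 19, and training is at study month 23. The part of the window that precedes training is 23 − (e + 19) = 4 − e months: 4 months at e = 0, 3 at e = 1, 2 at e = 2, 1 at e = 3, and none from e = 4. Because examinations follow training, the first children have a usable window of 23 to 29 months, while those enrolled from month 4 keep 19 to 29. The effective window therefore depends on enrolment date.

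**3. Against the analysis rule.** Follow-up length is not a baseline variable, so a rule triggered by significant differences at T0 can never select it. Age could be selected, but only if the groups differ significantly, whereas Co-variates says it needs adjusting for.

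**4. Size.** The plan gives no accrual rate. Assumption: linear accrual to the planning mean of 6.9 dmfs at age 6 (72 months), starting at some age between 0 and 36 months.
- Rate = 6.9/72 = 0.096 to 6.9/36 = 0.192 dmfs per month.
- Over 10 months: 0.96 to 1.92 dmfs, against 1.5 to 2.0.
- Assumed 3-month difference in group mean timing: 3 × 0.096 = 0.29 to 3 × 0.192 = 0.58 dmfs, which is 14 to 29% of the 2-dmfs planning difference.

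**5. Effect on the error rate.** Planned SD 6.2; 165 × 0.80 = 132 children analysed per group; the 15% excess read as a design effect of 1.15.
- SE = 6.2 × √(2 × 1.15/132) = 0.82.
- Bias/SE = 0.29/0.82 = 0.35 to 0.58/0.82 = 0.70.
- Two-sided rejection under no effect = Φ(−1.96 + b) + Φ(−1.96 − b), with b = bias/SE: about 6% at the lower end and 11% at the upper, instead of 5%. This is a normal approximation to the planned count model.

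**6. Equal spread.** If T2 is uniform over the 10 months in both groups, the timing component has SD = rate × 10/√12 = 0.28 to 0.55 dmfs. The total SD becomes √(6.2² + 0.28²) = 6.21 to √(6.2² + 0.55²) = 6.22 dmfs, so the loss of power is negligible.

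**The case against.** Both groups share the same T1 and T2 schedule, and step 6 shows that common variation costs almost nothing. Harm needs a difference in mean timing between groups, and the documents give no reason to expect 3 months. The extra intervention contacts, a visit at one month and a telephone call about a month later, supply no evident route to T2 timing nearly two years on. The 10-month span also needs both tolerances at their limits in the same direction. All of this stands: it limits the size of the problem but does not repair the rule.

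A term for follow-up time is often left to the SAP, which is not shown. That is fair, and its absence alone would be no finding. The point is that the adjustment rule the article does state selects on baseline differences and so excludes follow-up length, while the statement on age differs between two sections.

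Three stronger readings are tempting and not supported:
- **Examinations by uncertified dentists.** A reader might infer from the early window that uncalibrated primary-outcome data are allowed. The clinical outcome section places examinations after training and requires a kappa threshold for certification. What remains is a scheduling conflict for the earliest children.
- **No anchor for a child who misses T1.** The nominal 24-month date from T0.0 still applies; only the tolerance is undefined.
- **A larger error rate.** Taking all 6.9 dmfs as accrued in 24 months gives 0.29 per month and, with a 3-month difference, an error rate of about 18%. That presumes no caries at entry. The plan admits children with dmft below 4 and extracts baseline dmfs for adjustment, and 6.9 is a population mean while this trial excludes higher-caries children.

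**Conclusion.** The point holds as a badly fixed rule, not as evidence of bias. Read as plus or minus, the tolerances accept the primary examination anywhere from 19 to 29 months (20.5 to 27.5 on the narrower reading). They leave the tolerance undefined after a missed T1, and they conflict with the training date for children enrolled in the first four months. The stated adjustment rule cannot bring in follow-up length and makes age conditional.

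Under assumed linear accrual of 0.10 to 0.19 dmfs per month, the permitted span is worth about 1.0 to 1.9 dmfs, the same order as the effect sought. The 0.3 to 0.6 dmfs shift and the 6 to 11% error rate rest further on an assumed 3-month difference in group means; the actual difference is unknown and may be near zero. Given a cumulative outcome, non-random allocation and unblinded scheduling, this should be corrected, since the correction is cheap.

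**What to change.** 1. In Contact moments, define the T2 tolerance from T0.0, so that it applies whether or not T1 took place. Using the plan's own 3 months would give 21 to 27 months.
2. Reconcile that window with the training date in the clinical outcome section, stating how T2 is scheduled for children whose window opens before examiners are certified.
3. In Statistical analysis, include age at the T2 examination (or baseline age together with months since T0.0) in the primary count model for all children, whatever the baseline comparison shows. This also removes the inconsistency with Co-variates.

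The cost is a sentence or two of protocol text, a scheduling rule and one or two covariates built from dates the visits already generate. The downside is slightly less freedom to combine T2 with a regular check-up.

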#### Training of oral healthcare professionals

The dental therapists participating in the intervention group will receive training in the intervention. The training will consist of three half-day training sessions led by the research team, and will include interactive lectures on learning theory, behavioural psychology, responsive parenting and interview and counselling techniques. Mock meetings will be conducted to practice the interview method using role-playing exercises. Dental therapists will also be encouraged to video-record themselves when practicing the method with a parent or colleague. These video recordings will function as learning material for the second and third training session in which the group will be asked to give constructive feedback to each other. All materials and theories discussed during the training will be made available for the dental therapists in the form of a syllabus.

Dental practices in both the intervention and control group will separately be informed about the study procedures, which includes information on the recruitment of participants and methods of data collection, as well as information on the provision of care as usual and dental health education according to national guidelines [4, 28]. It is expected that this is standard procedure for practices, but the importance of adherence to the guidelines for this study will be emphasised.

### Outcome measures

The primary outcome of this trial, children’s dental caries experience after 24 months, are measured at T2. Secondary outcomes, namely ^1)^ parents’ self-efficacy (confidence) in brushing their children’s teeth when experiencing barriers, ^2)^ tooth brushing frequency in children, and ^3)^ children’s dental plaque scores, are measured at T0.0, T1 and T2. The intervention is considered successful when a 25% reduction in dental caries experience is observed in the intervention group in comparison to the control group, which equals a reduction of 1.5 to 2.0 dmfs. Tooth brushing-related outcomes are assessed to provide additional information on the intervention’s effect and on the pathways by which the intervention might affect children’s caries experience. If one of more tooth brushing-related outcomes are significantly more favourable in the intervention group compared to the control group, but dental caries experience is not reduced by at least 25%, the intervention is not considered successful.

### Data collection

#### Tooth brushing-related outcomes

Parents’ self-efficacy in brushing their children’s teeth

A validated questionnaire from Finalyson et al. [32] will be used to measure parents’ self-efficacy in brushing their children’s teeth when experiencing barriers. The questionnaire consists of a nine-item measure which inquires parents about their confidence in making sure children’s teeth are brushed before bedtime when the parent is ^1)^ under a lot of stress, ^2)^ depressed, ^3)^ anxious, ^4)^ feeling like not having the time (too busy), ^5)^ tired, ^6)^ worrying about other things in life, ^7)^ bothered by their child crying, ^8)^ bothered because their child doesn’t stay still when wanting to brush, ^9)^ told by their child that he / she doesn’t feel like brushing right now (Additional file 2). Possible responses range from ‘1’ (not at all confident) to ‘4’ (very confident). Responses to the nine questions will be summed and a mean score is calculated to generate a total self-efficacy score.
2.Tooth brushing frequency in children

Parents will be requested to complete a self-administered questionnaire which includes questions on the frequency of brushing their child’s teeth (‘not every day’, ‘once a day’, ‘twice a day’ and ‘three times a day’), skipping tooth brushing when the child doesn’t want to brush (‘always’, ‘often’, ‘sometimes’, ‘never’) and the use of fluoride toothpaste (Additional file 2). The questions are selected from a validated questionnaire from Pine et al. [33] and have been forth and back-translated and tested in the Dutch context [10].
3.Children’s dental plaque scores

Dental plaque indices are used to assess an individual’s level of plaque control, providing an indication of the efficiency of tooth brushing and the state of oral hygiene [34]. In this study, dental plaque accumulation in children will be assessed on the vestibular surfaces of the central and lateral incisors in the upper and lower jaw. The dental hygienist or therapist will apply disclosing solution on the tooth surfaces using a cotton swab, after which the child is asked to rinse once. A digital white-light photograph will be taken of the teeth in an end-to-end position using a smartphone camera, using lip and cheek retractors to allow good view of the teeth. All images will be captured within 2 min of disclosure to minimise colouring variation. The images will be manually scored using the modified Quigley & Hein index [34]. Dental plaque will be scored on three sites of each tooth (distal, buccal, mesial) on a 6-point scale from no plaque (score ‘0’) to more than 2/3rd of surface covered with plaque (score ‘5’). A mean plaque score will be computed by calculating the sum of scores divided by the total number of scored tooth surfaces. All images will be scored by one trained and calibrated examiner from the research team, and 10% of the images will be scored by a second examiner to assess the inter-examiner reliability. Both examiners will be blind to whether the image is taken at T0.0, T1 or T2, and in an intervention or control practice.

#### Clinical outcome: children’s dental caries experience

At T2, a clinical oral examination will be performed to assess children’s dental caries experience. The clinical oral examination will only include a visual inspection and no x-rays will be taken. Dental caries status will be assessed using the merged International Caries Detection and Assessment System (ICDAS) coding system [35], which classifies dental caries into sound (‘0’), initial stage of decay (‘A’), moderate decay (‘B’) or extensive decay (‘C’). In addition, the dmfs-index will be scored according to WHO Basic Methods for Oral Health Surveys [36]. The oral examinations will be performed by one dentist from each control or intervention practice, after they have received training from a certified ICDAS trainer for calibration and standardisation purposes. The training will be organised 23 months after inclusion of the first participants. During the training, the dentists’ intra- and inter-examiner reliability will be assessed; a minimum weighted kappa of 0.60 for both the intra and inter-examiner reliability is required to certify as an examiner [37]. In case of lower reliability scores, more training will be provided. The dmft and dmfs at baseline will be extracted from personal dental health records from the dental practice, in order to compare differences in dental caries experience between intervention and control children at baseline, and to adjust for potential differences in the analysis.

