#### Power calculation

The primary expected outcome of the study is a lower dental caries experience in the intervention group, compared to the control group, after 24 months. A power calculation indicated that a sample of 330 children will be required (165 children in each group) to detect a minimum difference of 2 decayed, missing and filled surfaces (dmfs) between the intervention and control group. This calculation is based on the following parameters: 80% power, a significance level of 5%, a mean dmfs of 6.9 ± 6.2 in 6-year-old children in the Dutch population [26], an expected loss to follow-up of 20 and 15% excess to account for clustering in the analysis. Further analyses indicated that a sample of 330 children will be amply sufficient to detect differences in tooth brushing-related outcomes.

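### Weighted kappa of at least 0.60, the only stated test for examiners, does not limit one-directional scoring by the single dentist who scores each practice

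*Protocol article*

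**What the plan says.** The section on the clinical outcome (children's dental caries experience) states: "The oral examinations will be performed by one dentist from each control or intervention practice". A certified ICDAS trainer calibrates these dentists first. To be certified, "a minimum weighted kappa of 0.60 for both the intra and inter-examiner reliability is required to certify as an examiner". A dentist who falls short is retrained: "In case of lower reliability scores, more training will be provided". No other criterion is given. The training comes 23 months after the first inclusions.

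The Blinding section says that the professionals who collect data cannot be blinded. The Outcome measures section counts the intervention a success at a 25% reduction, put at 1.5 to 2.0 dmfs. The Power calculation assumes "a mean dmfs of 6.9 ± 6.2 in 6-year-old children in the Dutch population" and adds "15% excess to account for clustering in the analysis", with no intracluster correlation (ICC). The Statistical analysis section adjusts all analyses for clustering within practices.

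**The concern.** The primary comparison is between average caries scores, so the examiner error that matters most is a consistent tendency to score high or low. Kappa compares a dentist's codes with a reference surface by surface. When most surfaces are sound, or most codes agree, a steady loss of a quarter of the lesions costs little kappa.

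Each dentist scores one practice only, so such a tendency cannot be separated from the practice. This has two consequences:

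- Tendencies that vary at random between dentists add between-practice variance and cost precision.
- A tendency that differs on average between the arms goes straight into the estimated effect.

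The second is the more serious. The examiners know their arm, and the Discussion accepts that volunteering intervention practices may be more engaged in prevention. The secondary plaque outcome has one blinded examiner and a 10% second reading; nothing comparable is described for the primary outcome.

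**Working it through.** **1. The plan's own figure.** Inputs from the Power calculation: difference 2, SD 6.2, 80% power, 5% level. Per arm, n = 2 × (z_α + 0.842)² × 6.2² / 2².

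- One-sided (z = 1.645): 119. Then 119 × 1.20 × 1.15 = 164.2, so 165 per arm and 330 in all, as stated.
- Two-sided (z = 1.96): 151, and 151 × 1.20 × 1.15 gives 209 per arm, which does not match. That is a separate issue. Here the 15% is taken as a design effect of 1.15.

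**2. Kappa of a dentist who under-scores a quarter of B/C surfaces.** Lesion mixes are assumed (sound/A/B/C), with all other codes correct. Weighted kappa = 1 − observed weighted disagreement / chance weighted disagreement.

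| Mix, % | B/C called A (linear, quadratic) | B/C called sound (linear, quadratic) |
|---|---|---|
| 88/5/3.5/3.5 | 0.93, 0.95 | 0.88, 0.86 |
| 60/15/12.5/12.5 | 0.91, 0.93 | 0.84, 0.81 |
| 25/25/25/25 | 0.85, 0.87 | 0.76, 0.69 |

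Lowest cell worked out: a quarter of B and of C is 0.0625 each. Observed disagreement = 0.0625 × 4/9 + 0.0625 × 1 = 0.0903; chance disagreement = 0.2917; kappa = 1 − 0.0903/0.2917 = 0.69. Every cell passes 0.60.

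False positives narrow the margin. With two categories and 25% missed, kappa is about 0.61 at specificity 0.95 and 7.8% of surfaces affected, and 0.53 at 5% affected.

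**3. Size of the shift.** 0.25 × 6.9 = 1.7 dmfs if every scored surface is open to the error, and about 0.9 if half of dmfs is filled or missing surfaces (assumed). As an illustration, if mean scoring differed by 10 percentage points between arms, the bias would be 0.10 × 6.9 = 0.69 dmfs, or about 0.35 on the half share.

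**4. Does this use up the 15%?** Design effect = 1 + (m − 1) × ICC, with ICC = (examiner SD in dmfs)² / 6.2². Completers per practice at 330 children: m = 330 × 0.8 / 40 = 6.6.

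- Allowance: ICC = 0.15/5.6 = 0.027, a between-practice SD of √0.027 × 6.2 = 1.01 dmfs, or 15% of 6.9. At m = 8 (ten recruited per practice, 20% lost) it is 0.91 dmfs, or 13%.
- Misses spread evenly over 0 to 25%: SD 0.50, ICC 0.0065, design effect 1.04.
- Half the dentists missing 25% and half none: SD 0.86, ICC 0.019, design effect 1.11.
- Even spread of ±25%: SD 1.00, ICC 0.026, design effect 1.14.
- Examiner SD of 20 to 25% of the mean: design effect 1.28 to 1.43. If only half of dmfs is affected, 1.07 to 1.11.

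**5. How a signed limit would behave.** Assume 40 B/C training lesions, 15% missed at random and as many false positives (6 expected). The net count has variance 40 × 0.15 × 0.85 + 6 = 11.1, SD 3.33. An unbiased dentist exceeds ±10% (±4 lesions) in 17 to 23% of cases and ±15% (±6) in 5 to 7%. The lower figures count whole lesions and the upper use the normal approximation.

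**The case against.** The examiners are trained by a certified trainer, tested both within and between examiners, and retrained if they fall short. Random differences between them are carried into the standard error by the planned cluster adjustment, and a tendency shared by all 40 does not add to clustering. These points stand, and they limit the harm from random shifts to lost precision.

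It is also fair that the pass figures describe a dentist with no other error. The training lesion mix and the kappa weights are not given, and enough false positives would fail the same dentist.

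A reader might go further and infer that examiner shifts alone exhaust the 15% allowance, so that the 80% power is lost. The documents do not support this. At 6.6 completers per practice, one-directional misses of up to a quarter stay within 1.15. Exceeding it takes an examiner SD of about 15% of the mean, over-scorers as well, or larger clusters, and the real spread is unknown. Halving the shift for filled or missing surfaces brings even an SD of 20 to 25% back inside. Nor do the power and examination sections contradict each other: one states no ICC and the other no examiner variance.

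Finally, a check on training cases cannot show what unblinded dentists do with their own patients. That also stands.

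**Conclusion.** The concern holds for the certification rule. A kappa threshold of 0.60 on its own lets through a dentist who under-scores a quarter of B/C surfaces (weighted kappa about 0.69 to 0.95 under the assumed mixes and no false positives). In that practice the shift can reach about 1.7 dmfs, of the order of the whole success margin, and less to the extent that dmfs consists of filled or missing surfaces. The 6.9 is the planning mean, not an observed value for this sample.

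The main risk is a mean shift that differs between arms. It would bias the effect, the cluster adjustment would not remove it, and no stated check would show it. Whether such a difference will occur cannot be judged from the documents. A loss of power below the planned 80% through examiner variation is possible but not shown. The improvement is worth making because it costs little.

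**What to change.** Keep the kappa rule. From the same ICDAS training scores, also compute each dentist's mean signed difference from the trainer in B/C surfaces, as a percentage of the trainer's count. Before the training, set a limit suited to the number of training lesions, for example ±15% or wider with about 40 lesions; ±10% would send too many unbiased dentists back. When the limit is exceeded, use the retraining already foreseen. Report the mean signed difference by arm with the primary result.

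The cost is one more statistic from scores the training already yields, with no added examiner or visit. A few unbiased dentists will repeat training by chance (about 5 to 7% at ±15% under the assumptions above). The check does not cover bias from unblinded scoring at the trial examinations themselves, and the report should say so.
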